## Abstract

**Background:**

Overweight and obesity are linked with Binge Eating Disorder (BED). Effective interventions to significantly reduce weight, maintain weight loss and manage associated pathologies like BED are tipically combined treatment options (dietetic, nutritional, physical, behavioral, cognitive-behavioral, pharmacological, surgical). Significant difficulties with regard to availability, costs, treatment adherence and long-term efficacy are present. Particularly Cognitive Behavioral Therapy (CBT) is the therapeutic approach indicated both in in-patient and in out-patient settings for BED. In recent years systemic and systemic-strategic psychotherapies have been implemented to treat patients with obesity and BED involved in familiar problems. Particularly a brief protocol for the systemic-strategic treatment of BED, using overall the strategic dialogue, has been recently developed. Moreover telemedicine, a new promising low cost method, has been used for obesity with BED in out-patient settings in order to avoid relapse after the in-patient step of treatment and to keep on a continuity of care with the involvement of the same clinical in-patient team.

**Methods:**

The comparison between CBT and Brief Strategic Therapy (BST) will be assessed in a two-arm randomized controlled clinical trial. Due to the novelty of the application of BST in BED treatment (no other RCTs including BST have been carried out), a pilot study will be carried out before conducting a large scale randomized controlled clinical trial (RCT). Both CBT and BST group will follow an in-hospital treatment (diet, physical activity, dietitian counseling, 8 psychological sessions) plus 8 out-patient telephone-based sessions of psychological support and monitoring with the same in-patient psychotherapists. Primary outcome measure of the randomized trial will be the change in the Global Index of the Outcome Questionnaire (OQ-45.2). Secondary outcome measures will be the percentage of BED patients remitted considering the number of weekly binge episodes and the weight loss. Data will be collected at baseline, at discharge from the hospital (c.a. 1 month after) and after 6-12-24 months from the end of the in-hospital treatment. Data at follow-up time points will be collected through tele-sessions.

**Discussion:**

The STRATOB (Systemic and STRATegic psychotherapy for OBesity), a comprehensive two-phase stepped down program enhanced by telepsychology for the medium-term treatment of obese people with BED seeking intervention for weight loss, will shed light about the comparison of the effectiveness of the BST with the gold standard CBT and about the continuity of care at home using a low-level of telecare (mobile phones).

**Trial registration:**

ClinicalTrials.gov Identifier: NCT01096251

## Background

One of the most important medical and public health problems of our time is represented by obesity [1]. It is widely considered as a chronic pathology and a risk factor for many medical complications such as endocrinological, pneumological, cardiovascular, and orthopedic diseases [2-8]. Overweight and obesity are also traditionally connected with Binge Eating Disorder (BED), psychopathology characterized by frequent and persistent episodes of binge eating with the key feeling of losing the control and the significative distress due to the absence of regular compensatory behaviors such as in the patients with bulimia [9]. Effective interventions to significantly reduce weight, maintain weight loss and reduce related pathologies like BED are tipically combined treatment options (dietetic, nutritional, physical, behavioral, cognitive-behavioral, pharmacological, surgical). Significant difficulties in these kinds of approaches have been underlined with regard to availability, costs, treatment adherence and long-term efficacy [10]. Even if the combined treatment options are the gold standard in weight loss, most overweight and obese individuals regain about one third of the weight lost with treatment within 1 year [11] and they will typically come back to baseline in 3 to 5 years [12-14].

About the psychological treatment of BED, Cognitive Behavioral Therapy (CBT) and Interpersonal Psychotherapy (IPT) are the psychotherapies more indicated in the Eating Disorder field [9]. Particularly CBT is the therapeutic approach indicated both in in-patient and in out-patient settings for BED [15-27].

The prevalence and spread of CBT is not under discussion, in recent years systemic, strategic and systemic-strategic psychotherapies have been implemented to treat patients with obesity and BED, overall when the pathology includes familiar characteristics and problems [26-30]. Particularly a brief protocol for the systemic-strategic treatment of BED, using overall the typical brief techniques such as the strategic dialogue, has been recently developed by Nardone and Portelli in the Handbook of Brief Strategic Therapy (BST) [31] and other contributions [32,33].

In order to deal with problems of weight regain and treatment relapses after 12-24-36 months, telemedicine, a new promising low cost method, has been used for obesity with BED in out-patient settings. This enhances the treatment after in-patients rehabilitation and keeps continuity of care through the involvement of the same clinical in-patient team [34-37].

Taking into account this scenario, we developed the STRATOB study (*Systemic and STRATegic psychotherapy for OBesity*), a comprehensive two-phase stepped down program enhanced by telepsychology for the medium-term treatment of obese people with BED seeking intervention for weight loss. The key aspects of the STRATOB study are the hospital-based intensive treatment and the continuity of care at home using a low-cost level of telecare (mobile phones). Many treatments delivered using new technologies, such as web-sites, e-mails, chat lines, videoconferences, UMTS mobile-phones and traditional telephones could represent a valid integration for traditional psychotherapy reducing expensive and time-consuming clinical visits and improving adherence to prescribed psychological, dietetic and medical treatments through extended monitoring and support [10,12,34,38-46].

This paper describes the design of the STRATOB study, a small scale two-arm randomized controlled clinical trial (RCT). The main aim of this study will be to compare the effectiveness of the BST [31-33] with the gold standard CBT [26,47-53] in a in-patient and telephone-based out-patient program for a sample of obese people with BED seeking treatment for weight reduction.

## Methods

The comparison between the CBT and BST will be assessed in a two-arm randomized controlled clinical trial. Participants will be randomly allocated in 2 groups:

1) CBT group: in-hospital treatment (diet, physical activity, dietitian counseling, 8 sessions of CBT) plus 8 out-patient telephone-based sessions of CBT-oriented psychological support and monitoring with the same CBT in-patient psychotherapists;

2) BST group: in-hospital treatment (diet, physical activity, dietitian counseling, 8 sessions of BST) plus 8 out-patient telephone-based sessions of BST-oriented psychological support and monitoring with the same BST in-patient psychotherapists;

The Medical Ethics Committee of Istituto Auxologico Italiano approved the study protocol and the Informed Consents.

The rehabilitation program considered in this study will have a total duration of 7 months and consists of two stepped down phases: in-patient (1 month) and out-patient (the following 6 months).

During the in-patient phase, participants will undergo an intensive four-week hospital-based and medically-managed rehabilitation program for weight reduction. Along this period, participants will live in a hospital located on a mountain highland and far away from towns and cities. Visits from family members and friends are allowed only in the afternoon. All patients will be placed on a hypocaloric nutritionally balanced diet tailored to the individual after consultation with a dietitian (energy intake around 80% of the basal energy expenditure estimated according to the Harris-Benedict equation and a macronutrient composition of about 16% proteins, 25% fat and 59% carbohydrates). Furthermore, they will receive nutritional counseling provided by dietitians, psychotherapy provided by psychologists-psychotherapists (well trained in CBT and BST approaches) and have physical activity training provided by physiotherapists.

Nutritional rehabilitation program aims to improve and promote change in eating habits and consists of both individual sessions (dietary assessment, evaluation of nutrient intake and adequacy, nutritional and anthropometric status, eating patterns, history of overweight, readiness to adopt change) and group sessions (45 minutes each session, twice a week, including: information on obesity and related health risks, setting of realistic goals for weight loss, healthy eating in general, general nutrition and core food groups, weight management and behavior change strategies for preventing relapse).

Psychotherapy will be provided twice a week in individual setting. CBT individual sessions, lasting 45 minutes each, are mainly based on the cognitive-behavioral approach described by Cooper and Fairburn [53] and emphasize the techniques of self-monitoring, goal setting, time management, prompting and cueing, problem solving, cognitive restructuring, stress management and relapse prevention. BST individual sessions, lasting 45 minutes each, are mainly based on the brief strategic approach described by Nardone and colleagues [31-33] and emphasize the techniques of working on "attempted solutions" (such as keeping control by abstaining from food and continuously striving to exert self-control with a subsequent loss of control), using reframing maneuvers, inducing fear of fasting rather then bingeing, understanding what is maintaining and worsening the problem, etc. (p. 105-105, [31]).

Physical activity will take place once a day except for week-end and consists of group programs (20 subjects) based on postural gymnastics, aerobic activity and walks in the open. In-patients with specific orthopedic complications will carry out individual activities planned by physiotherapists and articulated in programs of physical therapy, assisted passive and active mobilization and isokinetic exercise.

At the end of the in-patient step low to moderate weight losses will be expected and it is important to underline that weight loss is not the primary goal of the in-patient program (each patient is made clear about this point at the very beginning of the treatment). Beyond the medical management of metabolic risk factors for health such as type 2 diabetes, developing a sense of autonomy and competence will be the primary purposes of the in-hospital interventions. Skills and tools for change will be provided to patients and they will be supported in assigning positive values to healthy behaviors and also in aligning them with personal values and lifestyle patterns.

Just after discharge, participants will have 4 telephone calls with their in-patient psychotherapists along 2 months. From the 3rd to the 6th month sessions will be scheduled every 30 days. During tele-sessions, psychotherapists will test the out-patients' progress, their mood, the maintenance of functional alimentary and physical activity habits, the loss/increase of weight and will discuss about critical moments. Some research indicates that changes in behavior (eating and exercise) often follow discrete moments which have been variably described as life events or life crises [54]. Life events can lead to weight loss but also to weight gain and qualitative research shows that it is not the event per se that results in behavior change but the ways in which this event is appraised, interpreted and managed by the individual [55]. Psychotherapists (both CBT and BST) will have thus the opportunity to discuss with their patients in remote settings about the significant events during the telephone calls and will cognitively reconstruct dysfunctional appraisals in functional ways. In particular, phone-sessions with the psychotherapists will aim to consolidate strategies and abilities acquired during the in-patient phase, to improve self-esteem and self-efficacy, to support motivation, to prevent relapse and to provide problem-solving and crisis counseling.

As underlined, in the out-patient step of the STRATOB program great relevance will be given to the clinician-patient relationship as an important medium and vehicle of change [56]. After discharge, out-patients will begin to experience the autonomy and competence to change they will have developed during the in-patient phase and inevitably face resistances and barriers. Out-patients will be supported by telephone by the psychotherapists who will have attended them during the in-hospital phase in exploring resistances and barriers they experience and in finding functional pathways to cope. Furthermore, out-patients will be helped to experience mastery in terms of the health behavior change that needs to be engaged.

### Recruitment of the study population

One hundred consecutive female in-patients with obesity and BED in the age range of 18-65 years, who will be referred to a single clinical center (Saint Joseph Hospital - Istituto Auxologico Italiano IRCCS) for weight-loss treatment, will be asked and screened for admission to the study. Patients will be sequentially recruited.

### Inclusion and exclusion criteria

In-patients will be eligible when they will meet the following inclusion criteria at the admission to the hospital: 1) age between 18 and 65 years; 2) obesity according to the WHO criteria (BMI ≥ 30); 3) BED (DSM-IV-TR criteria) and 4) written and informed consent to participate. Exclusion criteria for the study are: 1) other severe psychiatric disturbance diagnosed by DSM-IV-TR criteria; 2) concurrent medical condition not related to obesity. SCID (Structured Clinical Interview for DSM-IV-TR Disorders) I and II [57] will be used as screening tools for psychiatric disorders and will be administered by an independent clinical psychologist as part of his work.

### Randomization procedure

All participants will be randomly assigned to the CBT or BST group. The randomization scheme will be generated using the Web site Randomization.com (http://www.randomization.com). Randomization will occur after the baseline measurements.

### Patient Assessment and Measurements

Primary outcome measure of the randomized trial will be the change in the Global Index of the Outcome Questionnaire (OQ 45.2).

Secondary outcome measures will be the percentage of BED patients remitted considering the number of weekly binge episodes and the weight loss. Data will be collected at baseline, at discharge from the hospital (c.a. 1 month after) and after 6-12-24 months from the end of in-hospital treatment.

Weight will be assessed with the participant in lightweight clothing with shoes removed on a balance beam scale.

Data collected at follow-up time points will be collected through tele-sessions.

### Psychological and behavioral assessment

Participants will complete the Outcome Questionnaire (OQ 45.2) - Italian translation and validation [58,59] at entry to the study and at discharge from the hospital with a self-report procedure. The number of weekly binge episodes will be assessed with a self-report procedure at entry to the study and at discharge from the hospital. At 6-12-24 month follow-up data will be collected via telephone during the tele-sessions.

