### Outcome Questionnaire (OQ 45.2)

The OQ 45.2 is a self report questionnaire developed by Michael Lambert in 1996 [60]. The OQ 45 items version is a measure of outcome and it is designed in order to collect repeated measures of patient progress during psychotherapy and after its conclusion. This instrument is one of the most used in psychotherapy research in the U.S. [61]. The OQ 45.2 is composed by 45 items that form 3 scales: Symptom Distress (SD), Interpersonal Relations (IR) e Social Role (SR), and a Global Index. The OQ 45.2 is proposed as a brief screening and outcome scale that tries to assess the subjective experience of a person, as well as the way he or she functions in the world [60]. The choice of this questionnaire has to take into account the need to measure a change in a short time (1 month of in-patient treatment) due to psychotherapeutic activities. The Italian version of the OQ-45.2 appears promising as a measure of general psychological distress, and it could be used to measure the psychotherapy outcome in routine clinical practice. So the Outcome Questionnaire-45 was developed as a brief measure of client progress in psychotherapy to address the need for accountability in the era of managed care and to improve upon extant outcome measures.

The investigator involved in administering and interpreting the OQ45.2 will be blinded to treatment assignment.

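### Follow-up OQ-45.2 and binge data are assigned to the treating therapists' tele-sessions, which contradicts the stated blinding of OQ administration, and those sessions end at month 6

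*Protocol article*

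**What the plan says.** All references are to the Protocol article.

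- **When data are collected.** Patient Assessment and Measurements lists baseline, discharge at about one month, and then "after 6-12-24 months from the end of in-hospital treatment". The primary outcome is the change in the OQ-45.2 Global Index; no primary time point is attached to it.
- **How follow-up data are collected.** Psychological and behavioral assessment says "At 6-12-24 month follow-up data will be collected via telephone during the tele-sessions". The Methods part of the Abstract has "Data at follow-up time points will be collected through tele-sessions", and Patient Assessment and Measurements has "Data collected at follow-up time points will be collected through tele-sessions". At entry and discharge, by contrast, the OQ-45.2 and the binge count are self-reported.
- **What the tele-sessions are.** Methods describes, for the BST arm, "8 out-patient telephone-based sessions of BST-oriented psychological support and monitoring with the same BST in-patient psychotherapists", with a matching sentence for CBT. The calls begin after discharge, 4 of them over two months; then "From the 3rd to the 6th month sessions will be scheduled every 30 days". The out-patient phase lasts six months.
- **Who is blinded.** The section on the OQ-45.2 says "The investigator involved in administering and interpreting the OQ45.2 will be blinded to treatment assignment".
- **What is analysed.** Sample size calculation and statistical analysis applies t tests to the OQ variables at every time point and a chi-square test to binge episodes at 6 months. Missing values other than weight are filled by carrying the baseline or last observation forward.

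**The concern.** The blinding statement covers administering the OQ-45.2 as well as interpreting it, and makes no exception for follow-up. The tele-session rule, stated three times, places follow-up data collection inside calls held by someone who is delivering one of the two treatments. A therapist cannot be blind to the therapy that he or she gives.

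The outcomes are patient-reported distress and binge frequency. Patients would be reporting them to the person who treated them, in calls where the Methods section deliberately stresses the clinician-patient relationship. This is a setting in which candid answers are hard to guarantee. The follow-up data also carry much of the trial's interest: the Discussion expects any difference in binge remission to appear at 6, 12 and 24 months, because patients do not face binge temptation in hospital.

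The second problem is timing. If the therapy calls have stopped, a rule that collects data during those calls gives no instruction for the later visits. Values not obtained there would be replaced under the carry-forward rule.

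**Working it through.** No sample-size figure is involved. The check is a session count, followed by a comparison of the stated rules.

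**1. Reproduce the stated number of sessions.** Inputs from Methods: 4 calls in the first two months after discharge, then one every 30 days from month 3 to month 6, that is at months 3, 4, 5 and 6.

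- Sessions = 4 + 4 = 8, which agrees with the 8 stated for each arm.
- Programme length = 1 month in-patient + 6 months out-patient = 7 months, which agrees with the stated total.
- The last session is therefore at month 6 after discharge.

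**2. Compare with the follow-up visits.** These are counted from the end of in-hospital treatment, the same origin as the calls.

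| Assessment | Stated collection | Scheduled tele-session? |
|---|---|---|
| Baseline | self-report | not applicable |
| Discharge | self-report | not applicable |
| Month 6 | in tele-session | yes, the last one |
| Month 12 | in tele-session | no; 12 − 6 = 6 months after the last |
| Month 24 | in tele-session | no; 24 − 6 = 18 months after the last |

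Of the four post-baseline assessments, three are assigned to tele-sessions and two of those have no session.

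**3. Is the OQ-45.2 part of the follow-up data?** Psychological and behavioral assessment names it only for entry and discharge and speaks of data in general at follow-up. Two other statements bring it in: Patient Assessment and Measurements gives a single visit schedule directly after listing the primary and secondary outcomes, and the analysis section tests OQ variables at all time points. Follow-up OQ-45.2 values are therefore required, and the only collection route stated for them is the tele-session.

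**4. Set the three rules side by side.**

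- (a) Follow-up data are collected during tele-sessions.
- (b) Tele-sessions are held by the patient's own arm-specific psychotherapist.
- (c) The person administering the OQ-45.2 is blinded.

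From (a) and (b), the follow-up OQ-45.2 is taken in a call held by an unblinded therapist. That is incompatible with (c) unless someone else administers it, and the text does not say so.

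**The case against.** The strongest reply is that no sentence says a therapist administers the OQ-45.2. The Methods list of what psychotherapists cover in the calls includes progress, mood, habits, weight and critical moments, but neither the questionnaire nor a binge count. The only person named as administering the OQ-45.2 is the blinded investigator, so a separate call by that investigator, loosely termed a tele-session, may be what is meant. This stands as a possible intention. It does not remove the conflict, because the text places collection during sessions that it defines as therapy calls. If a separate call is meant, the article has to say so.

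Several stronger readings are tempting and are not supported:

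- **That the primary comparison as a whole is compromised.** No primary time point is named. The OQ-45.2 section justifies the instrument partly by the need to detect change over the one-month stay. If the main comparison is baseline to discharge, this point does not reach it.
- **That the bias favours one arm or matches the planning effect of d = 0.2.** Both arms receive the same number of calls from their own therapists, and Psychotherapists and Treatment Fidelity describes training in both approaches without stating any allegiance. A differential bias of 0.2 SD would be an assumption chosen to equal the planning value; nothing in the document gives its size or direction.
- **That moving from self-completion to telephone biases the comparison.** The change applies to both arms, and reading the items aloud is itself an inference.
- **That the 12- and 24-month data will not be collected.** Collection at those visits is explicitly planned, by telephone. What is missing is a session of the kind named.

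A condensed article may leave call logistics to the full protocol. Here, however, the stated rules conflict with each other, so the point is not one of omitted detail.

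**Conclusion.** The point holds as a contradiction between stated rules. Followed literally, the tele-session rule has follow-up OQ-45.2 and binge data taken in calls by the treating, unblinded therapist, contrary to the blinding statement for the OQ-45.2. It also refers to sessions that do not exist at months 12 and 24.

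The extent is three of four post-baseline assessments for the collection rule and two of four for the absent sessions. This rests on reading tele-sessions in its defined sense and on the OQ-45.2 being collected at follow-up, which the analysis section requires. Baseline and discharge OQ-45.2 are unaffected. The consequence for the primary comparison depends on a time point that the article does not name, and no between-arm bias can be quantified from the document.

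The point should be settled before follow-up begins, since outcome data gathered unblinded or not obtained cannot be repaired in the analysis.

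**What to change.** - Amend the Methods part of the Abstract, Patient Assessment and Measurements, and Psychological and behavioral assessment so that OQ-45.2 and binge counts at 6, 12 and 24 months are collected outside the therapy calls. Either the blinded investigator already described in the OQ-45.2 section makes stand-alone calls, or patients complete the self-report form used at baseline and discharge. The self-report form also keeps the mode of administration constant.
- State the contact used at months 12 and 24, when no therapy calls are scheduled.
- Tell patients that their answers are not passed to their therapist, and ask them not to reveal their arm to the assessor.
- Reconcile weight separately. Patient Assessment and Measurements specifies a balance beam scale and also says that follow-up data come through tele-sessions. An assessment call cannot deliver a weighing on that scale, so the article should state how follow-up weight is obtained.

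**Cost.** This needs protocol wording plus 80 patients × 3 follow-ups = 240 short calls or forms at the planned sample size. The article does not say whether the blinded investigator has time for these contacts; the self-report form is the lighter option if not. If separate blinded calls were already intended, the OQ-45.2 and binge part reduces to a clarifying sentence.
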